A number of four to six focus groups each with GPs and patients, respectively, with a maximum of ten to twelve participants per group, and eight to twelve individual interviews each with GPs and patients are expected to be sufficient. Data collection will continue until reaching data saturation [42]. GPs will be recruited through addressing regional quality circles of GPs (association of GPs who meet regularly to share and reflect on their everyday practice [43]), representatives of practice and GP networks, the teaching and research practice network of the study institute, and from the NRW General Practice Research Network [44]. Patients will be contacted via self-help or rehabilitation groups in the Rhine-Ruhr region. In addition, study information in health care facilities and public institutions will be used to reach people who are preferably not members of self-help groups or cardiac sports groups. Experienced moderators from the study institute will conduct the focus group discussions. Data will be collected in an iterative cyclical process. Saturation marks the point in the iterative process of data collection and evaluation at which additional data collection does not lead to any further gain in knowledge according to the research question. The interviews and group discussions will be audio-recorded and transcribed verbatim, according to simple scientific transcription rules [45]. Postscripts document the atmosphere, the conversation process, interactions, specifics, and disruptions.

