### WP3: Systematic development of the GP training

WP3 focuses on the synthesis of results from WP1 and WP2 to inform the systematic development of a brief, single-session, tailored GP training on the delivery of PA advice to people with IHD according to the 3As method.

In a strategy workshop, results of WP1 and WP2 will be compared and connected, using visual representations (e.g., acyclic behaviour change diagrams [48]), discourse and expert consensus techniques.

The interdisciplinary study team, comprising experts in research on behaviour change, health services and public health, will develop a training manual in collaboration with GPs and patient representatives, with provisions for future adjustments for sustainability, such as online booster modules and good practice videos. The COM-B (capability, opportunity, and motivation-behaviour) model [35] will serve as theoretical framework for the development of the training, and the behaviour change taxonomy (BCT) will be used to describe active elements of the training [28]. According to COM-B, the interplay between capability (C), opportunity (O), and motivation (M) influence behaviour (B), and a specific behaviour in turn influences these factors [35]. The training will be developed to address “capability and motivation” by providing knowledge and practical skills to deliver PA advice. By using the 3As (ask/assess, advise, assist) method as a very brief, less time-consuming method of delivering advice, which can be more easily integrated into daily practice, the training will also aim to influence “opportunity”. The definition and description of potentially active training elements according to the BCT [28] will also be part of WP3. Training materials and case vignettes for simulated role-plays using simulation patients will be developed in collaboration with the “communication in medical education” team of the Heinrich-Heine University. Experienced GPs and peer-trainers from the study institute will review the training manual and didactic methods.

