## Phase II) Piloting of the intervention study and of the main evaluation study

### WP5: Pilot study

Based on preliminary work of the study team [22] and as recommended according to the MRC framework [31], a feasibility study testing the practicality of the planned evaluation study (WP6) is not considered necessary. Instead, a pilot study will be carried out to evaluate implementation outcomes, including the training of GP peer trainers, recruitment and randomisation processes, content and schedule of the training, materials, methods of data collection among patients and GPs including pre-tests of the study questionnaire and potential need for sample size adjustment. The pilot study will essentially function as a “scale model” of one study cycle of the planned pragmatic, two-arm, clustered randomised controlled trial (cRCT). For each study cycle, ten GP practices will be randomised (1:1) into either the intervention or control group. A study cycle is defined as a period of 5 weeks of face-to-face, practice-based data collection in people with IHD immediately following consultation with GPs who have been trained (intervention group, *n* = 5 practices) and a period of 5 weeks of face-to-face data collection in people with IHD immediately after consultation with GPs who have not been trained (control group, n = 5 practices). Per practice, approximately twelve people with IHD will be recruited, resulting in a pilot sample of 120 people with IHD.

A process evaluation with semi-structured, problem-centred individual interviews with GPs of the pilot study and with their patients with IHD who received PA advice will also be conducted. The aim is to understand: A) to what extent training contents could be implemented into practice, which factors facilitated or hampered the transfer, and how GPs experienced the delivery of very brief PA advice, and B) patients’ experiences with received advice, and their met and unmet needs. Experiences with the study procedures will be explored in both groups. Approximately six to eight interviews per group are expected to be sufficient. Data collection will continue until reaching data saturation [42] (for methodological details see WP2). Based on the insights gained from these interviews, study processes and the training manual will be further refined.

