It is expected that around twelve people with IHD can be recruited within a period of five weeks, hence a total of five study cycles (with a total of 25 control practices and 25 intervention practices) will be needed to reach the target sample of 600 people with IHD. Periods of data collection in both groups will be temporally close to each other to avoid influences by fluctuations in patient flow, but cannot be conducted in parallel due to logistical reasons. The potential bias which may arise from the presence of a researcher collecting data in the practices is assumed to be equally distributed over the study arms. Patients will be masked to the purpose of the study until the end of the data collection. Due to the pragmatic nature of the study, neither GPs nor researchers can be fully masked to the allocation of study arms. To mitigate the risk of contamination, standard operation data collection procedures will be developed, and researchers will not be involved in the delivery of the training.

The control group will not receive a "placebo" intervention as this may lead to lower participation rates and pose a risk of bias (e.g., if a training on the delivery of stop-smoking advice would be offered to controls, GPs might be sensitised to provide advice on other detrimental health behaviours). However, once data collection in their patients is completed, GPs of the control group will immediately be offered the same training as the intervention group. This approach will ensure high retention rates in the control group.

GPs who have not participated in a program to promote PA within the last 5 years will be eligible. There are no other inclusion or exclusion criteria for GPs.

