Patients will be enrolled in the study if they are ≥ 35 years old and if they have a clinical diagnosis of IHD according to International Classification of Diseases-10 I25.-I25.9. Due to data protection regulations, it will not be possible to learn about the presence of a clinical IHD diagnosis until the patient has provided written informed consent to participate. All consecutive patients willing to participate will therefore be screened during the study interview for a self-reported IHD diagnosis made by a physician, comparable to standards in health surveys [e.g., [2]]. Only participants screened positive for IHD will be interviewed on the study outcomes. All participants will be asked for their permission to verify their IHD screening result with the medical record obtained from the practice nurse. Only patients with a clinical diagnosis will be included in the final analyses. If the pilot study shows that there is a high level of correlation between self-reported IHD and validated IHD, strategies will be developed to include people who only report IHD in their self-report in the statistical analysis of the evaluation study (e.g., sensitivity analyses). The inability to provide informed consent (e.g., language barriers) and physical handicap impeding PA will be exclusion criteria for patients. GP practices will be recruited from the online register of the regional Association of Statutory Health Insurance Physicians NRW, and from the NRW General Practice Research Network [44].

With regard to a potential broader implementation and dissemination of the training, a qualitative process evaluation (comparable to WP5) with approximately eight to twelve GPs will accompany the cRCT to explore facilitators and barriers of GPs to the routine implementation of PA advice, including reimbursement strategies for its routine provision. In addition, semi-structured qualitative telephone interviews will be conducted in a subsample of 30 to 40 people with IHD who received PA advice from a GP of the intervention group on their motivation to become more active, and on barriers and facilitators to implement the recommendations of their GP into their daily lives, one month following the GP consultation (for methodological details see WP2 and WP5).

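### WP6 closes its GP eligibility list without saying whether GPs involved in WP2, WP3 or the pilot control arm may be randomised

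*Protocol article*

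**What the plan says.** The WP6 section of the protocol article gives one criterion for GPs: "GPs who have not participated in a program to promote PA within the last 5 years will be eligible". The next sentence closes the list: "There are no other inclusion or exclusion criteria for GPs". The article does not define what counts as such a programme and does not mention participants of the earlier work packages.

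GPs have contact with the project before WP6 in several ways:

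- **WP2** explores GPs' attitudes to and experiences of PA advice, and their training needs, in interviews and focus groups. "GPs will be recruited through addressing regional quality circles of GPs", and also through practice networks that include the NRW General Practice Research Network.
- **WP3** develops the training manual together with GPs, and "Experienced GPs and peer-trainers from the study institute will review the training manual and didactic methods".
- **WP5**, the pilot, is one cycle of the main design: "ten GP practices will be randomised (1:1) into either the intervention or control group", five per arm. It also covers the training of GP peer trainers.

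WP6 recruits practices from the regional physicians' register and "from the NRW General Practice Research Network", the network already used for WP2. The article describes the WP6 control arm as patients of GPs who have not been trained.

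**The concern.** The sample size rests on a 20% advice rate among GPs who have had no training. A GP who helped write or review the manual knows the intervention's content. A GP who spent an interview or focus group on PA advice has been prompted to think about it. An untrained pilot control has already been through the data-collection procedure. If such a GP is randomised to control, that practice's rate may lie above 20% and the estimated effect shrinks.

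The protocol accepts this kind of mechanism. In the WP6 section it rejects a placebo training for controls partly because training in smoking-cessation advice might sensitise GPs to advise on other health behaviours. Earlier discussion of PA advice itself is at least as close to the outcome. With 25 practices per arm, a few such practices could matter.

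**Working it through.** **1. Who the criterion reaches.**

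| GP group | Covered by the five-year criterion? |
|---|---|
| Pilot intervention GPs (WP5) | Probably: they received training to promote PA advice, within a project that lasts five years in all |
| Peer trainers | Plausibly, as they are themselves trained |
| Pilot control GPs (WP5) | Unclear: covered if trained afterwards, which is stated for WP6 controls but not for WP5 |
| GPs developing or reviewing the manual (WP3) | Not plainly |
| GPs in interviews or focus groups (WP2) | Not plainly |

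The criterion is also written per GP, while practices are randomised. The status of a practice with one exposed GP is therefore not fixed.

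**2. How many GPs.** The WP2 text gives 8–12 GP interviews and 4–6 GP focus groups of at most 10–12. The ceiling is 8 + 4×10 = 48 to 12 + 6×12 = 84 GPs. These figures use maximum group sizes, and Table 1 can be read as 4–6 groups for GPs and patients together, so the real number may be well below. The pilot adds ten practices. No number is given for WP3. How many of these would join WP6 is not stated anywhere.

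**3. Baseline power by the plan's method.** Inputs from the WP6 section: 20% versus 33%, 300 patients per arm, ICC 0.05, 12 patients per practice. Alpha is not stated there; I assume 5% two-sided.

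- Design effect: 1 + 0.05×11 = 1.55, as stated.
- Odds ratio: (0.33/0.67)/(0.20/0.80) = 1.97, as stated.
- Effective n per arm: 300/1.55 = 193.5.
- s0 = √(2×0.265×0.735/193.5) = 0.0449; s1 = √((0.20×0.80 + 0.33×0.67)/193.5) = 0.0444.
- Power = Φ[(0.13 − 1.96×s0)/s1] = Φ(0.948) = 82.8% (83.4% with unpooled variance).

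The plan states at least 85%. That small gap is a separate matter, and this point does not rest on it; 82.8% serves only as the reference.

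**4. Illustration of dilution.** Let k of 25 control practices be exposed, each carrying a fraction e of the 13-point effect. The shift is d = 0.13×e×k/25, and the control rate becomes 0.20 + d. Two cases bracket what happens in the other arm: either the intervention rate stays at 33% (training adds nothing further to exposed GPs), or it also rises by d (the same number of exposed practices there, with a fully additive effect).

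| e | k | Control rate | Power, intervention held at 33% | Power, equal rise in both arms |
|---|---|---|---|---|
| 0.5 | 1 | 20.26% | 81.2% | 82.6% |
| 0.5 | 2 | 20.52% | 79.4% | 82.4% |
| 0.5 | 3 | 20.78% | 77.6% | 82.2% |
| 1 | 1 | 20.52% | 79.4% | 82.4% |
| 1 | 2 | 21.04% | 75.7% | 81.9% |
| 1 | 3 | 21.56% | 71.6% | 81.5% |

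At half effect the loss is 1.6 to 5.2 points in the first case and 0.2 to 0.7 points in the second. Both k and e are assumptions.

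**The case against.** **Condensed article.** WP6 is described only briefly, its details may change after the pilot, and a fuller protocol is promised on OSF. Eligibility detail could sit there. This would carry weight if the article were merely silent. But the article states that no further criterion exists, so a later document could add one only by contradicting it.

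**Randomisation balances prior exposure.** In expectation it does, and the Discussion makes that argument for GP attitudes. Equal numbers of exposed practices do not by themselves preserve the contrast, though. It is preserved only if the training adds its full increment on top of what exposed GPs already do. That cannot be settled from the documents, so the objection stands to this extent: dilution is possible, not shown.

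**WP2 teaches nothing.** Its interviews and focus groups explore attitudes, barriers and needs, not how to deliver the 3As, and one interviewed GP is not a whole practice. This stands. It makes the full-effect rows of the table implausible for WP2 participants.

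**Stronger readings that the documents do not support.** A reader might infer that GPs trained in the pilot can be randomised; the five-year criterion most naturally excludes them. A reader might take 48–84 as the count of exposed GPs; it is a ceiling. A reader might expect power of 72–79%; that needs whole control practices at the trained level and no gain at all from exposure in the intervention arm. Nor is it shown that these GPs are the likeliest to join, since WP6 also recruits from the physicians' register and the Discussion plans to approach less motivated GPs.

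**Conclusion.** The point holds as a defect in a stated rule. Followed literally, the WP6 criteria do not plainly exclude GPs from WP2, GPs who developed or reviewed the training in WP3, or untrained pilot controls, and a shared recruitment network makes overlap realistic. For GPs trained in the pilot the only defect is an undefined term.

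The consequence is a plausible bias towards the null of unknown size. At half the training effect in 1 to 3 of 25 control practices, power lies between 77.6% and 82.6%, against a reference of 82.8%, depending on whether exposure also lifts the intervention arm. The range rests on an assumed number of exposed practices, an assumed carry-over and a two-sided 5% test. It shows the order of magnitude and predicts nothing.

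**What to change.** Replace the closing sentence on GP criteria in the WP6 section with one that says:

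- practices are not eligible for WP6 if any of their GPs took part in WP2, helped develop or review the training in WP3, took part in either arm of WP5, or serves as a peer trainer;
- the OptiCor pilot training counts as a programme to promote PA.

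Wording the rule at practice level matches the unit of randomisation. The WP4 expert workshop need not be on the list: it selects patient outcomes as attributes for the choice experiment and does not deal with how GPs give advice.

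The cost is one sentence, and the article reports that WP6 had not yet begun when it was submitted. The downside is a slightly smaller recruitment pool: the ten pilot practices and the practices of the GPs from WP2 and WP3. No additional patients or staff are needed.

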**Fig. 2 Fig2:**
[figure not shown]
Study flow of the planned cluster randomised controlled trial (O = no training). A study cycle consists of 10 weeks of data collection: 5 weeks patients of “control” and 5 weeks in patients of “intervention” general practitioners (GPs). In total there will be five cycles resulting in 50 practices (25 intervention and 25 control practices)

As described in WP1, we calculate with an estimate of 20% of patients who report the receipt of brief PA advice during their GP visit without the GP having been trained. Another study showed that a brief single-session GP training can increase patient-reported rates of GP-delivered stop-smoking advice by 20%-points on average [52]. Training GPs to deliver PA advice might be more challenging, e.g., because PA recommendations are more complex than simple advice on smoking cessation methods. Training on PA advice is thus declared to have a clinically relevant effect if higher rates of delivered PA advice of at least 13%-points can be achieved in the intervention group (33%) as compared to the control group (20%), corresponding to an odds ratio of 1.97. Sample size calculation is based on the standard χ2-test in a four-fold-table and a multiplicative correction (= 1 + 0.05*(12–1) = 1.55, i.e., assuming an intraclass correlation coefficient of 0.05 and twelve IHD patients/practice) by the design effect to account for clustering. Including a total of 600 people with IHD in 50 practices (25 per study arm) will yield a power of at least 85% in the primary analysis of the intervention effect in a logistic regression model with a random intercept effect accounting for the nested design, while adjusting for patient and practice characteristics.

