### Analyses WP6

A detailed study and analysis protocol will be published at OSF prior to the statistical analyses. The data analysis will follow the hierarchical clustered structure of the study (patients nested within practices). Logistic mixed-effects regression models will be applied to analyse the primary outcome, with a fixed effect for the group (intervention versus control) and a random intercept for the practices. The same model will be used on the secondary outcomes. Models will be adjusted for pre-defined potential confounders: patients’ age, sex, education, level of PA, and BMI. All patients will be included in an intention-to-treat analysis. Based on experiences from another cRCT [52], missing data on the primary outcome is assumed to be minimal as data will be collected through face-to-face interviews. However, multiple imputation will be applied to impute missing data if needed.

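### The WP6 analysis population is not pinned down: patients who refuse the record check drop out after randomisation, and 600 is not tied to a counting stage although the power has no reserve

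*Protocol article*

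**What the plan says.** In the protocol article, the eligibility paragraph of WP6: Main evaluation study makes a clinical diagnosis an entry condition: "Patients will be enrolled in the study if they are ≥ 35 years old and if they have a clinical diagnosis of IHD" (ICD-10 I25). Because of data protection, that diagnosis cannot be looked up before consent. Consenting patients are therefore screened by self-report during the study interview, and "Only participants screened positive for IHD will be interviewed on the study outcomes". Then "All participants will be asked for their permission to verify their IHD screening result with the medical record", which comes from the practice nurse. The resulting restriction is "Only patients with a clinical diagnosis will be included in the final analyses". If the pilot shows a high correlation between self-reported and validated IHD, "strategies will be developed to include people who only report IHD in their self-report in the statistical analysis of the evaluation study", with sensitivity analyses as the example.

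The section Analyses WP6 says "All patients will be included in an intention-to-treat analysis" and does not define the population.

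The sample size paragraph reads "Including a total of 600 people with IHD in 50 practices" and claims power of at least 85%. The following paragraph expects about twelve people with IHD per practice in five weeks, giving a target sample of 600.

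**The concern.** The eligibility paragraph and the analysis section each give a rule for who is analysed, and neither refers to the other. Three things are left open.

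- **Patients who cannot be checked.** The record check needs permission. A patient with true IHD who declines cannot be shown to have a clinical diagnosis, so a literal reading removes that patient. Screening takes place in an interview held after the consultation, so this loss comes after randomisation and after exposure to a trained or untrained GP.
- **The analysis that would show the effect of that loss.** Including self-report-only patients depends on a pilot correlation for which no measure or cut-off is given.
- **The count.** If fieldwork stops at twelve interviewed patients per practice, the analysed number will be below 600. If it stops at twelve confirmed patients, it will not. The article does not say which applies.

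At stake are the definition of the primary result, the ability to see whether verification loss differs between arms, and the power.

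**Working it through.** **Inputs from the WP6 sample size text:** 20% against 33%; ICC 0.05; 12 patients per practice; 25 practices and 300 patients per arm; chi-square test multiplied by a design effect. The significance level is not stated, so two-sided 5% is assumed. The share of interviewed patients confirmed in the record, f, is not given, so values are assumed.

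**The plan's own figures**
- Odds ratio = (0.33/0.67) / (0.20/0.80) = 1.97, as stated.
- Design effect = 1 + 0.05 × (12 − 1) = 1.55, as stated.
- Effective n per arm = 300 / 1.55 = 193.5.
- Power = Φ{[0.13 × √n − 1.96 × √(2 × 0.265 × 0.735)] / √(0.20 × 0.80 + 0.33 × 0.67)}. With n = 193.5 this is Φ{(1.809 − 1.223) / 0.617} = Φ(0.948) = 82.8%.
- Variants at two-sided 5%: unpooled variance 83.4%, arcsine 83.1%, log odds ratio 82.0%, continuity-corrected 79.7%. None reaches 85%. A one-sided 5% test would give 89.7%, but the article does not mention one.
- For 85% with the pooled formula, 206 effective patients per arm are needed: 2 × 206 × 1.55 = 638.6, or about 639 analysed.

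**If 600 is the number interviewed.** All 50 practices are kept and the loss is spread evenly. Cluster size is 12f, design effect is 1 + 0.05 × (12f − 1), and effective n per arm is 300f divided by that design effect.

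| f (assumed) | Analysed | Design effect | Effective n per arm | Power |
|---|---|---|---|---|
| 1.00 | 600 | 1.55 | 193.5 | 82.8% |
| 0.95 | 570 | 1.52 | 187.5 | 81.7% |
| 0.90 | 540 | 1.49 | 181.2 | 80.3% |
| 0.80 | 480 | 1.43 | 167.8 | 77.2% |
| 0.70 | 420 | 1.37 | 153.3 | 73.4% |

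The cost of verification is the difference from 82.8%: 82.8 − 80.3 = 2.5 points at 90% confirmed and 82.8 − 77.2 = 5.6 points at 80%. The rest of the distance to 85% exists before any patient is excluded.

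**If 600 is the number confirmed.** Power stays at 82.8%, and the interviews needed rise to 600 / 0.90 = 667 or 600 / 0.80 = 750.

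**The case against.** A reader might infer that the two population statements flatly contradict each other. The documents do not support that. A clinical diagnosis is an enrolment criterion, and data protection only delays the check. The intention-to-treat sentence can be read as covering all eligible patients in their practice's arm, and removing someone whose record shows no IHD is compatible with intention-to-treat. This part of the objection stands. It does not cover the patient who refuses the check, because no ineligibility has then been found.

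A reader might also infer that verification will differ by arm because practices are unmasked. The article does not show this. Its masking statement concerns GPs and researchers, patients are masked to the study's purpose, and it does not say who judges the record or whether the check follows the outcome questions. Differential loss is possible but not demonstrated.

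On the count, the phrase people with IHD leans towards confirmed patients, and on that reading verification costs no power. That is fair, but the counting stage remains unstated.

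Finally, WP6 is described only briefly, the pilot may lead to a sample size adjustment, and a detailed analysis protocol is announced. Those documents may settle the details. However, the article itself states the restriction, the intention-to-treat rule and the conditional inclusion. The analysis protocol is promised only before the statistical analyses, which can be after recruitment.

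**Conclusion.** The point holds as a gap in definition, not as a contradiction. The primary population is not named, patients who refuse the record check are lost after randomisation under a literal reading, and the analysis that would include them has an undefined trigger.

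The power has no reserve: about 83% with all 600 analysed, and about 80% or 77% if 600 are interviewed and 90% or 80% are confirmed. It would be wrong to attribute the whole drop from 85% to verification; its share is about 2.5 to 5.6 points. These figures rest on a two-sided 5% level, assumed confirmation rates and even loss across practices and arms. If 600 already counts confirmed patients, only the roughly two-point gap to the stated 85% remains.

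The change should be made. According to the article WP6 had not started, so it is cheap at this stage.

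**What to change.** 1. In Analyses WP6, name one primary population, analysed by the allocated arm of the practice, and make the eligibility paragraph match. State how patients with a refused or impossible record check are handled.
2. Pre-specify the analysis of all screen-positive, interviewed patients as a fixed sensitivity analysis that does not depend on the pilot result. Report confirmation and refusal counts by arm.
3. State that 600 and twelve per practice count confirmed, analysed patients, with the interview target raised using the pilot's confirmation rate; or restate the power for the expected analysed number. In either case state the significance level and correct the claim of at least 85%.

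No rule on the date of diagnosis relative to randomisation is needed.

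**Cost:** rewording and one extra model run on data already collected, a slightly less favourable power figure, and possibly some patients without IHD in the sensitivity set. If 600 is fixed as the confirmed number, more interviews are needed.
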